**Fig. 2 Fig2:**
[figure not shown]
Study period

### Statistical analysis

The assumption of this trial is to match the results in adherence to intention-to-treat analysis. Patient demographic data and baseline characteristics will be presented with the use of descriptive statistics. For the summary of continuous data, we plan to apply minimum and maximum values, medians, means, standard deviations and quartiles. A summary of categorical variables will be presented as distribution (with the use of percentage and numbers). We plan to analyse the primary outcome, which is the PCS SF-36, by Wilcoxon’s test and general linear regression. We expect data to be non-normally distributed.

For the secondary outcomes, we plan to use the χ^2^ test for dichotomous variables and Wilcoxon’s test as well as regression analyses for ordinal data. Time-to-event data will be compared with log rank test.

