**Methods:**

This is a multi-centre, single-blinded, randomised controlled trial. The study population includes patients admitted to ICU units after major oncological gastrointestinal surgery that require supplemental parenteral nutrition. After initiation of enteral nutrition, the intervention group receives remaining daily requirement via supplemental parenteral nutrition on the first day of ICU stay while the control group is not supplemented parenterally until the seventh day of ICU stay while enteral nutrition is gradually increased.

Primary endpoint: long-term quality of life measured in the physical component score (PCS) of SF-36 questionnaire at 3 and 6 months after ICU admission.

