### Hypothesis

We hypothesise that early goal-directed supplementation of proteins in SPN may significantly increase the number of points in the physical component score (PCS) at 3 and 6 months after admission to ICU in the population of critically ill patients after oncological surgery of the gastrointestinal tract.

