### Outcomes

#### Primary endpoint

The long-term quality of life will be measured by the physical component of the 36-SF questionnaire assessed by a phone call at 3 and 6 months after admission to the ICU (License number QM047431 CT198126 OP073545 OGSR).

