### Rationale

According to the data presented by Allingstrup et al. [9] we estimated that 200 patients are needed to show a 15% relative reduction in the primary outcome (physical component of SF-36 score at 6 months) corresponding to a difference of 5.5 points (minimal clinical important difference defined as half a standard deviation from the observed dataset in the presented study) between the intervention and the control group at a significance level of 0.05 and a power of 80%. The calculations were based on a PCS of 37.5 (SD 10.65) among survivors from their data. The PCS SF-36 did not differ between the intervention and control groups at 6 months in the general ICU population in this study. Moreover, we increased the number of patients in our study to 220 assuming a 10% loss to follow-up among survivors from ICU. We hypothesised that early SPN might influence the long-term outcome of critically ill patients after oncological surgery of the gastrointestinal tract that constituted only 6% of the intervention group and 12% of the control group of the study mentioned above.

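### The protocol gives two definitions of the primary endpoint (3 and 6 months; 6 months only) and two unranked tests, so no single result decides the trial

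*Protocol article*

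**What the plan says.** **Time point.** The Methods part of the abstract gives the primary endpoint as "long-term quality of life measured in the physical component score (PCS) of SF-36 questionnaire at 3 and 6 months after ICU admission". The Primary endpoint section agrees: "physical component of the 36-SF questionnaire assessed by a phone call at 3 and 6 months after admission to the ICU". The Hypothesis is framed the same way, in that early supplementation "may significantly increase the number of points in the physical component score (PCS) at 3 and 6 months after admission to ICU". The sample size Rationale differs. It identifies the primary outcome as "physical component of SF-36 score at 6 months" and applies the 0.05 significance level and 80% power to that comparison.

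**Method.** The Statistical analysis section states: "We plan to analyse the primary outcome, which is the PCS SF-36, by Wilcoxon’s test and general linear regression". The next sentence reads: "We expect data to be non-normally distributed". Neither method is named as leading, and no time point is mentioned.

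The article contains no testing order, no division of alpha between time points, and no statement of whether one or both time points must be significant.

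**The concern.** The two definitions cannot both hold. With two time points and two methods, up to four results could be put forward as the primary one. Nothing written down in advance would show that the reported one was not chosen after the data were seen.

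Two things are at stake. First, the 5% error rate is protected under some readings and exceeded under others. Second, a split result has no agreed interpretation, whether between 3 and 6 months or between Wilcoxon and regression. Splits are realistic: with a true effect of half the planned 5.5 points at both times and SD 10.65, the two time points disagree on significance in about 25% to 33% of simulated trials (assumed correlation 0.7 to 0.5).

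This is not detail that can be left to an analysis plan. The primary time point belongs in the protocol, and here a later plan would have to overrule one of the protocol's own statements.

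**Working it through.** **Inputs from the protocol.** Alpha 0.05, power 80%, difference 5.5 points, SD 10.65, 200 patients before loss to follow-up and 220 after (sample size Rationale); 1:1 allocation (Sample size). Baseline PCS is collected (Participant data collection).

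**Assumptions.** Two-sided testing, because the protocol does not state sidedness. Wilcoxon's test is taken as the two-group rank-sum test. The correlation between 3- and 6-month PCS is not given, so a range is used.

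**1. The plan's own figure.** Per arm, n = 2 × [(1.960 + 0.842) × 10.65 / 5.5]² = 58.9, so 59 per arm and 118 in total. The stated 200 is not reproduced at 80% power; on these inputs 100 per arm gives about 95% power. That is a separate matter. It is relevant here only because it shows that the fix needs no extra patients.

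**2. Either time point counts, one method.** Under no effect, the error rate is 1 − P(|Z₃| < 1.96 and |Z₆| < 1.96), with Z₃ and Z₆ bivariate normal with correlation r. With independence it would be 1 − 0.95² = 9.75%.

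| r | Either time point | Both time points |
|---|---|---|
| 0.4 | 9.3% | 0.7% |
| 0.5 | 9.1% | 0.9% |
| 0.7 | 8.3% | 1.7% |
| 0.8 | 7.8% | 2.2% |
| 0.9 | 7.0% | 3.0% |

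The last column is 5% + 5% minus the middle column. It applies when there is no effect at either time. If there is an effect at one time only, requiring both still cannot exceed 5%, because the null time point must itself pass at 5%.

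**3. Either time point and either method counts.** The two methods use the same data, so the independence figure for four tests (1 − 0.95⁴ = 18.5%) does not apply. Simulation of null trials (100 per arm, 20,000 runs per setting) gives the chance that at least one of the four p-values is below 0.05:

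| Data and regression | r = 0.5 | r = 0.7 |
|---|---|---|
| Normal, unadjusted | 11.1% | 10.3% |
| Normal, baseline-adjusted | 13.8% | 13.2% |
| Skewed (log-normal), unadjusted | 13.1% | 11.6% |
| Skewed (log-normal), baseline-adjusted | 15.1% | 13.2% |

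The correlation of baseline with follow-up PCS is assumed to be 0.5. The simulation standard error is about √(0.11 × 0.89 / 20,000) = 0.2 percentage points.

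**4. 6 months alone decides.** With one method the rate is 5% by design. If either method may count, it is about 6% (normal data, unadjusted regression) and 5.4% to 8.5% over all settings tried.

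**5. Cost of keeping both time points primary.** At alpha 0.025 each, n = 2 × [(2.241 + 0.842) × 10.65 / 5.5]² = 71.3, so 72 per arm and 144 evaluable in total, below the planned 200. Power at 100 per arm and alpha 0.025 is about 92%. This assumes the same effect and SD at 3 months, for which the protocol gives no figures.

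**The case against.** A reader might infer that the trial's error rate is simply 10%, or that four primary p-values, each at 0.05, are planned. The document supports neither. It gives no number of tests and no alpha per test; its only alpha stands in the sample size Rationale, beside 6 months. The Hypothesis can be read as requiring an increase at both time points, which by one method keeps the error rate under 5%. The Rationale can be read as letting 6 months alone decide, which gives 5% by one method. The regression may also be meant as an adjusted estimate beside the Wilcoxon test and not as a second chance of success. All of this stands, and it makes the inflation conditional.

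It is also fair to say that the second method matters less than the second time point. On normal data without adjustment, the two time points take the rate from 5% to about 8% to 9%, and the second method adds about two percentage points.

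Finally, the sentence expecting non-normal data may explain why Wilcoxon is listed first, so a reader might infer that Wilcoxon decides. The text does not say so, but nor does it give grounds for insisting on regression.

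None of this removes the contradiction. That several readings are defensible is the defect.

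**Conclusion.** The point holds as a contradiction over the primary time point, together with a primary analysis that names two methods and ranks neither. The time-point conflict is the firmer part; the unranked methods are secondary. Confidence is high for the inconsistency. The numerical consequence is conditional on the success rule, and the figures above 5% rest on assumed correlations, two-sided testing and, for the method comparison, assumed data shapes. An error rate of about 10% belongs to the most permissive reading and is not a property of the plan as written. It should be settled before any outcome data are examined, since the primary claim currently has no single defined test.

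**What to change.** 1. In the abstract, Hypothesis and Primary endpoint sections, make PCS at 6 months the single primary endpoint, in line with the sample size Rationale. Make PCS at 3 months a key secondary endpoint.
2. If both time points are to stay primary, state either that both must be significant or that Holm's procedure applies. Requiring both lowers the power of the primary claim below that at 6 months alone.
3. In the Statistical analysis section, name one deciding test before data are seen and label the other a supporting analysis. Regression adjusted for the baseline PCS already collected is a reasonable option; so is Wilcoxon, given the expected non-normality. The choice is the authors'.

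**Cost.** Wording only for items 1 and 3. No power is lost at 6 months, because that is the comparison the trial was sized for. The price is that a significant 3-month result alone could no longer support the primary claim.

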**Discussion:**

To our knowledge, this is the first trial to investigate the influence of early supplemental parenteral nutrition on long-term quality of life after major oncological gastrointestinal surgery. We assume that, particularly in this population of patients, early supplemental parenteral nutrition may increase the long-term quality of life. The study construction also allows establishment of patients’ PCS SF-36 score prior to surgery and mean change in PCS SF-36 score during the recovery period, which is rarely seen in studies on critically ill patients.

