## Methods

### Assignment of intervention

#### Enrolment procedure

All study participants will be enrolled from surgical departments by anaesthetic residents during presurgical assessment according to the inclusion and exclusion criteria (Table 1 and Fig. 1). Prior to entry, the patient, next of kin or legal representatives will need to sign the consent forms.

**Table 1 Tab1:** Eligibility criteria

Inclusion criteria	Exclusion criteria	

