### Participant data collection

Participant background data of age, sex, medical history, primary diagnosis, weight, height, body mass index and baseline PCS SF-36 will be collected.

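### Pre-surgery PCS is collected but not named in the primary analysis, and neither of the two primary methods is designated as deciding

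*Protocol article*

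**What the plan says.** All references are to the protocol article; no statistical analysis plan is at hand.

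- **Statistical analysis**, on the primary outcome: PCS is to be analysed "by Wilcoxon’s test and general linear regression. We expect data to be non-normally distributed". No covariates are listed and neither method is ranked above the other.
- **Statistical analysis**, on baseline data: "Patient demographic data and baseline characteristics will be presented with the use of descriptive statistics". This section states no other use for them.
- **Participant data collection**: "baseline PCS SF-36 will be collected", among the background data.
- **Enrolment procedure**: "All study participants will be enrolled from surgical departments by anaesthetic residents during presurgical assessment". A score before surgery is therefore obtainable.
- **Abstract, Discussion**: the design is said to allow "establishment of patients’ PCS SF-36 score prior to surgery and mean change in PCS SF-36 score during the recovery period", which the authors describe as rare in studies of the critically ill.
- **Rationale** (sample size): the target is a difference of 5.5 points at 6 months, with SD 10.65, significance level 0.05 and power 80%.

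**The concern.** The article presents the pre-surgery score as a strength of the design, but the stated primary analysis gives it no role. Of the two methods named, Wilcoxon's test on follow-up scores has no place for a covariate. The regression could carry baseline PCS but is not tied to it. The remark about non-normal data leans towards the test that cannot use it.

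Two things are at stake. The first is precision: a patient's physical function before surgery may predict part of the follow-up score, and removing that part narrows the interval for the treatment effect and takes out chance imbalance in baseline PCS. The second is clarity. Two primary methods with no order between them can disagree, and a choice made after the data are seen would be open to challenge. The sample size is also framed as a difference in points. A regression coefficient estimates that directly; a Wilcoxon p-value does not.

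**Working it through.** **Inputs from the document (Rationale):** difference 5.5 points, SD 10.65, significance level 0.05 (taken as two-sided), power 80%, 200 patients before the allowance for loss to follow-up, allocation 1:1. **Assumed:** correlation r between pre-surgery and follow-up PCS, tried from 0.2 to 0.6.

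**1. The plan's own figure.** n per arm = 2 × (1.960 + 0.842)² × 10.65² / 5.5² = 58.9, so 59 per arm and 118 in total. The stated 200 is not reproduced. That is a separate matter; here it shows only that 200 analysed patients leave room to spare.

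**2. Power without adjustment, 100 analysed per arm.** Standard error = 10.65 × √(2/100) = 1.506. Then 5.5 / 1.506 = 3.652, and 3.652 − 1.960 = 1.692, which gives power 95.5%. The difference detectable with 80% power is 2.802 × 1.506 = 4.22 points. The 95% interval half-width is 1.960 × 1.506 = 2.95 points.

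**3. Effect of adjustment.** Residual variance is multiplied by (1 − r²). An unadjusted comparison of means therefore needs 1/(1 − r²) times the patients. The half-width and the detectable difference are multiplied by √(1 − r²).

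| r (assumed) | 1 − r² | Equivalent extra patients | Half-width, points | Detectable at 80% power, points | Power for 5.5 points |
|---|---|---|---|---|---|
| none | 1.00 | – | 2.95 | 4.22 | 95.5% |
| 0.2 | 0.96 | 4% | 2.89 | 4.13 | 96.1% |
| 0.3 | 0.91 | 10% | 2.82 | 4.03 | 96.9% |
| 0.4 | 0.84 | 19% | 2.71 | 3.87 | 97.9% |
| 0.5 | 0.75 | 33% | 2.56 | 3.65 | 98.8% |
| 0.6 | 0.64 | 56% | 2.36 | 3.38 | 99.5% |

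**4. Against Wilcoxon's test.** Step 3 compares means, so it carries over to Wilcoxon only approximately. A simulation with 99 per arm (110 less 10%), a true shift of 4.26 points and 3,000 runs per setting gave this power:

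| Data | r | Wilcoxon | Baseline-adjusted regression |
|---|---|---|---|
| Normal | 0.3 | 78% | 82% |
| Normal | 0.5 | 80% | 90% |
| Normal | 0.6 | 76% | 93% |
| Skewed (gamma) | 0.3 | 86% | 83% |
| Skewed (gamma) | 0.5 | 85% | 89% |
| Skewed (gamma) | 0.6 | 86% | 93% |

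Wilcoxon ignores baseline, so its variation across r is simulation noise. Adjusted regression is ahead except with skewed data at r = 0.3. A repeat with robust standard errors showed the same pattern. With stronger skew, Wilcoxon stayed ahead at moderate correlation too.

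**The case against.** The strongest reply is that the article does not exclude baseline PCS. It names a general linear regression and is silent on covariates, and a covariate list is commonly left to an analysis plan that is not shown. With a treatment term alone, that regression would be little more than a t-test, so naming it is at least compatible with adjustment. This stands against any claim that the primary analysis ignores baseline PCS. It does not answer the rest: the article itself fixes two primary methods, one of which cannot use baseline, and leaves open which decides.

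Other stronger readings that a reader might infer are not supported:

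- *That a definite number of patients is being wasted.* The document gives no correlation, and surgery plus an ICU stay between the two measurements could make it low.
- *That the trial lacks power without adjustment.* Step 2 shows otherwise for 200 analysed. An unadjusted comparison of randomised arms is also valid, since its standard error already allows for chance imbalance.
- *That change from baseline is the planned primary analysis.* The abstract only says the design allows mean change to be established. With equal variances, a change score has variance 2(1 − r) times that of the raw score, so it is worse when r is below 0.5. That matters only if it were made the main comparison.
- *That every patient will have a baseline score.* The article says only that it will be collected.

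**Conclusion.** The point holds as an inexpensive improvement to the analysis, not as an error that threatens the trial. Pre-surgery PCS is collected, the primary analysis does not name it, and the deciding method is open. Against an unadjusted comparison of means, adjustment is worth about 4% to 56% more patients for r from 0.2 to 0.6. With 200 analysed, that shortens the interval half-width from 2.95 points to between 2.89 and 2.36.

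These figures rest on the assumed r, on the document's SD of 10.65, and on 200 patients providing a score. The percentage gain does not depend on that last number, but the interval widths and the power do. Against Wilcoxon's test the gain is approximate, and it can vanish or reverse with skewed data, most readily at low correlation. The case for regression then rests on its estimate in points, which can be set against the 5.5-point target, and on its control of baseline imbalance.

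**What to change.** In the Statistical analysis section, replace the sentence on the primary outcome with wording such as:

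*Follow-up PCS will be analysed by linear regression on treatment group and baseline PCS, with robust standard errors, at 3 and at 6 months (6 months being the time point used for the sample size). The treatment coefficient with its 95% confidence interval is the deciding result. Wilcoxon's test will be reported as a supporting analysis.*

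Robust standard errors relax the assumption of equal variance, and with about 100 patients per arm the expected non-normality is not in itself a reason to give up a comparison of means. If marked skew is expected and a rank-type primary analysis is preferred, proportional-odds regression with the same two terms keeps baseline PCS in the model.

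The cost is one or two sentences, to be fixed before outcome data are seen by arm. No new data, visits or patients are needed.

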#### Secondary endpoints

A.During the 7-day treatment period in both treatment arms:
EN route intolerance (inability to administer up to 60% of protein needs on day 3 via EN route)Change from baseline in ultrasound measured thickness of diaphragm on days 1, 3 and 5 of ICU stayProtein deliveryEnergy intakeInsulin doseBlood glucose profileOrganic phosphorus levelB.During the 28-day treatment period in both treatment arms:
8.Change from baseline in the Sequential Organ Failure Assessment (SOFA) score9.Duration of mechanical ventilation10.Length of stay in the ICU11.ICU mortality12.Length of stay in hospital13.Hospital mortality14.New onset of hospital-acquired infection (defined according to the Centers for Disease Control and Prevention surveillance definition as a localised or systemic condition resulting from an adverse reaction to the presence of an infectious agent(s) or its toxin(s), with no evidence that the infection was present or incubating at the time of admission to the acute care setting)15.Antibiotic-free days

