#### Clinical testing data

Prior to enrolment, haemoglobin, platelet, Na^+^, K^+^, Ca, Cl^–^, Mg^2+^, P, triglyceride, alkaline phosphatase, aspartate aminotransferase, alanine aminotransferase, gamma glutamyl transferase and bilirubin levels, International Normalised Ratio, and activated partial thromboplastin time as well as presence of HIV, hepatitis B virus or hepatitis C virus will be assessed.Daily from days 1 to 7, haemoglobin, leukocyte, platelet, lactic acid, bicarbonate, urea, creatinine, bilirubin, alanine aminotransferase, aspartate aminotransferase, gamma glutamyl transferase, alkaline phosphatase, glucose, phosphorus, Na^+^, K^+^, Ca^2+^, Cl^–^, Mg^2+^, C-reactive protein, and procalcitonin levels as well as peripheral capillary oxygen saturation (SpO_2_), the arterial oxygen partial pressure to fractional inspired oxygen ratio (PaO_2_/FiO_2_), blood pH, partial pressure of carbon dioxide in arterial blood (PaCO_2_) and fluid balance will be measured.Daily from days 1 to 28 (or until discharge), the SOFA score will be measured.On days 1 and 7 of ICU stay, albumin and total proteins will be measured.On days 1, 3 and 5 of ICU stay, ultrasonographic assessment of the thickness of diaphragm will be performed.

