#### Treatment and support in-hospital data

All performed surgeries will be laparoscopic or opened abdominal/thoracic surgery. The surgical sites will be grouped into oesophageal procedures, gastric procedures, bile duct, liver or pancreatic procedures, small bowel procedures, colonic procedures, and rectal procedures.

Postoperative surgical course will be assessed for postoperative complications according to the 7-grade Clavien–Dindo classification.

The level of organ support and pharmacotherapy required will be assessed according to duration of CRRT and mechanical ventilation, antibiotic administration, gastric antisecretory agents, prokinetic agents, catecholamines and insulin dose (per 24 h).

The name of EN or PN, the target volume, received volume, energy intake, protein intake, intolerance to EN or PN support, and the decrease or discontinuation of nutritional support will be assessed.

The use of invasive devices such as central catheters, urinary catheters, enteral route devices and endotracheal tubes, with the dates of insertion and removal, will be recorded. All those parameters, treatments and devices will be controlled until day 28 or until discontinuation, whichever occurs first.

The occurrence of hospital-acquired infections such as ventilator-associated pneumonia, bacteraemia, catheter-related infections or urinary tract infections will be recorded.

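### SOFA and diaphragm thickness are change-from-baseline endpoints, but the plan states no adjustment for the day-1 value; a baseline-adjusted regression as main analysis would be more precise at almost no cost

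*Protocol article*

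**What the plan says.** The Secondary endpoints section of the protocol article lists "Change from baseline in the Sequential Organ Failure Assessment (SOFA) score" for the 28-day period, and a change from baseline in ultrasound diaphragm thickness for the 7-day period.

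The Clinical testing data section gives the schedule. For SOFA: "Daily from days 1 to 28 (or until discharge), the SOFA score will be measured". For the diaphragm: "On days 1, 3 and 5 of ICU stay, ultrasonographic assessment of the thickness of diaphragm will be performed". Both endpoints therefore have a day-1 value and at least one planned later value.

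The Statistical analysis section sorts the secondary outcomes by type. Dichotomous variables get a χ² test and time-to-event data a log rank test. In between stands "Wilcoxon’s test as well as regression analyses for ordinal data". The section does not say which variables enter the regression, and it does not mention the baseline value as a covariate.

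**The concern.** Two analyses are named side by side, and neither is marked as the main one for the two change endpoints. Only the Wilcoxon test is specific enough to carry out as written. On these endpoints it would compare raw changes between arms without adjustment.

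Subtracting the baseline treats the relation between day 1 and follow-up as if its slope were exactly one. When the slope is below one, as is usual for a measurement that varies within patients, subtraction over-corrects and adds noise. Regression on the day-1 value estimates the slope instead.

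What is at stake is precision, not validity. The Objective section makes short-term clinical outcomes part of the trial's purpose, and these two endpoints are its measures of organ function and of muscle. A wider interval than necessary makes a real difference easier to miss.

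**Working it through.** The document states no figure for the analysis of these endpoints, so there is none to reproduce.

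**Inputs**
- Endpoint form: change from baseline (Secondary endpoints).
- Baseline: the day-1 value, the first one scheduled (Clinical testing data).
- Sample size: 220, or 110 per arm (Sample size).
- Correlation r between the day-1 and follow-up values: not given. Assumed range 0.3 to 0.8.
- Standard deviation: not given. Taken as equal at the two times, and set to 1.

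**Formulas** (variance per patient, relative to the follow-up value alone)
- Raw change: 1 + 1 − 2r = 2(1 − r).
- Follow-up adjusted for day 1: 1 − r².
- Ratio: 2(1 − r)/(1 − r²) = 2/(1 + r).

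**Results**

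| r (assumed) | Raw change | Adjusted | Ratio | Interval width, √ratio | 220 patients on raw change equal this many adjusted, 220(1 + r)/2 |
|---|---|---|---|---|---|
| 0.3 | 1.40 | 0.91 | 1.54 | 1.24 | 143 |
| 0.5 | 1.00 | 0.75 | 1.33 | 1.15 | 165 |
| 0.7 | 0.60 | 0.51 | 1.18 | 1.08 | 187 |
| 0.8 | 0.40 | 0.36 | 1.11 | 1.05 | 198 |

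The raw-change analysis would need 54%, 33%, 18% or 11% more patients for the same precision. The last column assumes that all 220 contribute both values, so it illustrates the scale and does not forecast the trial.

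**If the two standard deviations differ.** Let s0 be the SD on day 1 and s1 the SD at follow-up. The variance of the change is s0² + s1² − 2r·s0·s1 = (s0 − r·s1)² + s1²(1 − r²). The second term is the adjusted variance and the first cannot be negative. The ratio is therefore never below 1, and it equals 1 only when s0 = r·s1, that is, when the slope of follow-up on day 1 is exactly one. The direction of the result does not depend on the equal-variance assumption; its size does.

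**Limit of the algebra.** These are variances of mean comparisons. A Wilcoxon test on the change against a regression on ranks will not follow them exactly, so the ratios are approximate for skewed data.

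**The case against.** The strongest reply is that regression is already named and could carry the day-1 value. That is true: the article does not exclude adjustment. The point is only that it neither states adjustment nor says which of the two analyses leads. It is also fair to say that covariates are often left to a full protocol or an analysis plan, neither of which is shown. This limits the point to an improvement of the stated analysis; it does not make it an error. Finally, the sentence quoted refers to ordinal data. SOFA fits that description, but diaphragm thickness is continuous, and its link to this sentence is an inference from the lack of any other suitable test in the section.

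Three stronger readings are tempting, and the document supports none of them.

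- **That the plan forces testing day by day, or pooling of days as if they were separate patients.** A reader might infer this because SOFA and thickness are measured repeatedly, as are the daily laboratory values and insulin dose, while a Wilcoxon test takes one value per patient. But that one value can be a mean, a maximum or a single change, and the section mentions neither daily tests nor pooling. In simulations with no true effect (100 per arm, 2,000 runs, 2 to 27 values per patient), one Wilcoxon test on each patient's mean rejected in 4.3% to 6.0% of runs, consistent with the nominal 5%. Error rates for daily or pooled testing would describe analyses that the plan does not prescribe.
- **That the day-1 value is left out.** It is not: a change from baseline subtracts it. What is not stated is its use as a covariate.
- **That the baseline reading may follow allocation.** The text does not place it before or after, but the study-period figure is not shown, so silence in the text proves nothing.

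**Conclusion.** The point holds as a modest gain in precision. For SOFA and diaphragm thickness, a Wilcoxon test on raw change is valid but less efficient than a comparison adjusted for the day-1 value. The variance ratio is 1.54, 1.33 and 1.18 at correlations of 0.3, 0.5 and 0.7, and shrinks to 1.11 at 0.8. These figures rest on assumed correlations, on equal variances at the two times, on day 1 being the baseline, and on an approximately linear relation. The plan as written does not inflate the false-positive rate, and the primary endpoint is not affected.

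**What to change.** In the Statistical analysis section, add a sentence for the two change-from-baseline endpoints. The main analysis is a regression of the follow-up value on arm with the day-1 value as covariate, on ranks or a log scale if the data are skewed. Name in advance one time point or one per-patient summary for each endpoint. Day 5, the last scheduled scan, would serve for the diaphragm. For SOFA, the chosen point or summary should take into account that scoring stops at discharge, so patients contribute different numbers of days. Keep Wilcoxon's test on the change as a sensitivity analysis.

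The cost is a few lines of text and little programming. No new measurements or patients are needed, because the day-1 values are already scheduled. The downside is a modest model assumption about the relation between day 1 and follow-up, and the retained Wilcoxon test gives a check on it.
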